### Assessments

The presence and indications for the catheter use will be extracted from the medical records in combination with observations of the admitted patients. During the day of measurement the indication of the urinary and/or intravenous catheter and some patient variables will be collected. If there is an unclear indication of a catheter, the investigator will contact one of the healthcare workers (HCWs) to verify this information.

After discharge, the occurrence of catheter-related infections (see Table 3 for definitions) [31], with diagnostics and treatment, or other catheter-related complications (measured in registry and by investigator), the number of catheter days, reinsertion rate, use of alternatives for an indwelling urinary catheter (continence garments, condom catheters, intermittent straight catheterization), reason for admission, Charlson comorbidity index [32], duration of hospital (and ICU) stay, readmission within 30 days after discharge, and mortality (in hospital or within 30 days after discharge) will be collected from (electronic) medical- and nursing records. Furthermore, the nurse-to-patient ratios and the clinical work experience of residents will be collected.

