### Appropriate use of catheters

We defined a list of valid indications for urinary and intravenous catheter placement, based on the literature (Table 1) [26–29]. All other indications are defined as inappropriate.

**Table 1 Tab1:** List of appropriate indications

Urinary catheter	Peripheral intravenous catheter	Central intravenous catheter
Acute urinary retention or bladder outlet obstruction (≥150 cc)	Delivery of peripherally compatible infusate (IV fluids and medications), at least once in 24 h	Delivery of non-peripherally compatible infusate (e.g., irritants or vesicants), regardless of proposed duration of use
Accurate measurements of urinary output in critically ill patients required for treatment	Transfusion of blood and blood products	PICC : delivery of peripherally compatible infusate, with a duration of use which will likely confine ≥ 6 days^b^
Volume measurements of urine output aim for diagnostics (24 h urine), which cannot be assessed by other collection strategies	Injection of contrast fluids	Invasive hemodynamic monitoring or requirement to obtain central venous access in critically ill patients -Nontunneled CVC : duration of use will likely confine < 15 days -PICC : duration of use will likely confine ≥ 15 days
Assist in healing of open sacral or perineal wounds in patients with urinary incontinence	Intravenous access for cardiac dysrhythmia	PICC : Delivery of cyclical or episodic chemotherapy that can be administered through a peripheral vein, provided that the proposed duration of such treatment is ≥3 months
Continuous bladder irrigation for hematuria	PIVC : duration of use will likely confine ≤ 5 days	Frequent phlebotomy (every 8 h), provided that the proposed duration of such use is ≥6 days
Patient requires prolonged immobilization	Midline : duration of use will likely confine ≤ 14 days^a^	PICC : Intermittent infusions or infrequent phlebotomy in patients with poor/difficult peripheral venous access, provided that the proposed duration of such use is ≥ 6 days
Palliative care for terminally ill if needed		PICC: For infusions or palliative treatment during end-of-life care
Pre- or postoperative according (local) protocol		Tunneled catheter or port : preferred if proposed duration is ≥ 31 day

^a^Use of PIVCs is preferred over use of midlines for infusion of peripherally compatible infusates up to 5 days

^b^Use of PIVCs or midlines is preferred over use of PICCs for infusion of peripherally compatible infusates up to 14 days

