### Primary and secondary endpoints

The primary endpoint is the percentage of patients with an inappropriate indication for urinary and intravenous catheter on the days of data collection. Secondary endpoints are catheter-related infections and other complications, catheter reinsertion rate, use of antibiotics, length of hospital stay (and ICU) in days, in hospital mortality, and costs of the de-implementation strategy and the main healthcare costs.

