### De-implementation strategy

We will use a bundle of interventions (Table 4), since it is known that multiple and well-organized interventions result into better improvements. The main intervention is the dissemination of the list of appropriate indications (Table 1), which will restrict the insertion of urinary and intravenous catheters by physicians and nurses. The recommendation will be to remove the catheters without or with an expired valid indication. A local ‘champion’ (one of the leading physicians) will be appointed to be responsible for the interventions in his or her department. The intervention period will start with a kick-off meeting, where a list of baseline data of the intervention hospital in comparison with the other study hospitals will be presented as a competitive feedback report [33]. If desired, feedback reports per department could be sent by e-mail to local investigators. Thereby two educational meetings about insertion, care and maintenance of urinary and intravenous catheters will be applied to change HCWs behavior. Furthermore, HCWs will be encouraged and reminded to remove inappropriate catheters by posters, pocket cards and e-mail messages. In addition to other studies, patients will be actively supported by education material to participate in their treatment.

**Table 4 Tab4:** De-implementation strategy

Interventions of de-implementation strategy
List of appropriate indications
Local ‘champion’
Kick-off meeting, including competitive feedback report of baseline data
Education meeting for healthcare workers
Education materials (e.g., posters, pocket cards)
Patient education materials
Optional interventions based on baseline data and local conditions per hospital

Subsequently, all impeded and promoted factors of this de-implementation strategy for both HCWs and patients will be evaluated by direct observations and interviews. Additional prevention strategies could be applied based on these affecting factors and local conditions in the different hospitals.

If this de-implementation strategy prove to be effective, persistent awareness of the local ‘champion’ in combination with recurrent surveillance of the appropriate use of catheters and catheter-related infections will improve the sustainability. Thereby the de-implementation rule “No indication = Remove catheter” will be recommended in national guidelines and local protocols.

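### Ward staff consulted about unclear indications are taught the scoring list only after baseline, so their answers may shift the primary endpoint at the interruption without any catheter being removed

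*Protocol article*

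**What the plan says.** All references are to the protocol article; the SAP is not at hand.

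- **Endpoint** (in the section that lists the endpoints): "The primary endpoint is the percentage of patients with an inappropriate indication for urinary and intravenous catheter on the days of data collection". The Abstract counts catheters rather than patients; the point is the same either way.
- **Scoring rule** (Appropriate use of catheters): Table 1 lists the accepted indications, and "All other indications are defined as inappropriate".
- **Source of the indication** (Assessments): "The presence and indications for the catheter use will be extracted from the medical records in combination with observations of the admitted patients". For the remainder: "If there is an unclear indication of a catheter, the investigator will contact one of the healthcare workers (HCWs) to verify this information".
- **Intervention** (De-implementation strategy): "The main intervention is the dissemination of the list of appropriate indications", that is, Table 1. It comes with educational meetings and a kick-off meeting at which each hospital's baseline results are set against those of the others. In addition, "HCWs will be encouraged and reminded to remove inappropriate catheters by posters, pocket cards and e-mail messages".
- **Timing** (Study design and setting): eight months of baseline measurement, a four-month transition in which the strategy starts and nobody is enrolled, then eight months of follow-up measurement.
- **Analysis** (Statistical analysis; Discussion): segmented regression, adjusted for confounders, autocorrelation and secular trend. The Discussion acknowledges that there is no control group.

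**The concern.** The primary endpoint does not count removed catheters. It is a label that depends on the reason attributed to each catheter. For unclear cases, one input to that label is what a ward worker says when asked. Before the interruption that worker has not been given the study list. Afterwards the worker has been taught it and has seen the hospital compared with others. The procedure is the same in both periods, but the informants are not in the same state of knowledge.

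If a trained worker more often gives a reason that happens to be on the list, the recorded percentage falls while the same catheters stay in. Because the change in informants coincides with the intervention, the model has no means of telling it from a real effect. At stake is how far a reported level change can be read as fewer unnecessary catheters.

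**Working it through.** **Step 1. The plan's own figures.** The Sample size section assumes 40% inappropriate use for urinary catheters and 50% for peripheral intravenous catheters (PIVC), a 25–50% relative reduction, 80% power and alpha 0.05. It gives 91–376 and 66–284 patients per period. A two-sided comparison of two proportions with continuity correction gives:

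- 40% vs 20%: 91; 40% vs 30%: 376 (both match)
- 50% vs 25%: 66 (matches); 50% vs 37.5%: 262, or 284 if 37.5% is rounded to 38%

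So the lower end of the target is 40% to 30% for urinary catheters and 50% to 37.5% for PIVC. These are the yardsticks used below.

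**Step 2. What changes at the interruption.**

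| | Baseline | After transition |
|---|---|---|
| Scoring list | Table 1 | Table 1 |
| First source | Record and observation | Record and observation |
| Unclear cases | Ask a healthcare worker | Ask a healthcare worker |
| Has that worker been taught Table 1 by the study? | No | Yes |
| Has the hospital been compared with others? | No | Yes |

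Only the last two rows change, and they change together with the intervention.

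**Step 3. Which entries are open to this.** Some Table 1 entries can be checked against the record or the patient: an infusion within 24 hours, transfusion, contrast injection, bladder irrigation, an open wound. Others rest on a stated need or expectation: "Patient requires prolonged immobilization" for urinary catheters, and the expected length of use for several intravenous lines. A change in answers is most plausible for the second group.

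**Step 4. Size, under assumptions.** The article gives neither of these shares:

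- u = share of inappropriate catheters whose indication is unclear before contact (assumed 10%, 30%, 50%)
- r = net extra share of those given a listed reason only after training (assumed 50%)

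With true inappropriate use p unchanged, the apparent later percentage is p × (1 − u × r), so the apparent relative reduction is u × r.

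| u | r | u × r | Urinary, from 40% | PIVC, from 50% |
|---|---|---|---|---|
| 10% | 50% | 5% | 38% | 47.5% |
| 30% | 50% | 15% | 34% | 42.5% |
| 50% | 50% | 25% | 30% | 37.5% |

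Only the last row reaches the lower end of the target.

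**Step 5. Chance of a significant improvement with no real change.** For a two-sided 5% test of two proportions with n per period, the chance is Φ{[(p1 − p2) − 1.96·√(2p̄(1 − p̄)/n)] / √[(p1(1 − p1) + p2(1 − p2))/n]}. Example, urinary, last row, n = 410: (0.10 − 1.96 × 0.0333)/0.0331 = 1.05, so 85%.

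| u × r | Larger planned n (410 urinary / 300 PIVC) | Smaller planned n (105 / 75) |
|---|---|---|
| 5% | 9% / 9% | 5% / 5% |
| 15% | 43% / 45% | 14% / 15% |
| 25% | 85% / 87% | 33% / 34% |

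With no shift at all, the figure would be 2.5% (half of 5%). The planned analysis is segmented regression, so these values are indicative only.

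**Step 6. What the model can do about it.** The shift is absent from the baseline series, so the baseline trend carries no information on it. Adjusting for secular trend and autocorrelation therefore leaves it in place, and it is reported as part of the level change.

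**The case against.** The case on the other side is substantial, and it rules out several stronger readings.

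- **A reader might infer that ward staff decide the endpoint.** The text does not say so. Record and observation come first, contact is a fallback to verify, and nothing says that a verbal answer overrides documented facts. Many Table 1 entries can also be checked. This stands: only the unclear, judgement-based cases are exposed.
- **A reader might infer that the bias favours the strategy.** That is plausible but not shown. Untrained staff may already offer listed reasons at baseline, and staff taught to remove catheters without a valid reason may admit more readily that there is none. Then r could be near zero or negative.
- **A reader might infer that staff carry the list on pocket cards.** The article says only that the cards remind staff to remove catheters; their content is not given.
- **A reader might put the spurious effect at the whole 25% target.** That takes 10 percentage points, which at r = 50% means that 20% of all urinary catheters are unclear and inappropriate, i.e. 0.20/0.40 = half of all inappropriate ones. The pilot cited in the Background points elsewhere: 89.2% of initial indications were appropriate, and most had lapsed after 2–3 days. Those are known indications that expired, not unclear ones.
- **A reader might infer that nothing in the study can reveal the problem.** Catheter days are collected (Assessments). Pure relabelling would leave them unchanged, so they are a partial check. They are not a named endpoint, however, and do not protect the primary one.
- **Form fields and sensitivity models belong in a fuller document.** True, and their absence from an article is not the finding. The finding is the stated rule combined with the stated intervention. A later analysis plan cannot recover a pre-contact classification that was never recorded.

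**Conclusion.** The point holds as a risk of unknown size. Unclear indications go to people whose knowledge of the scoring list changes at the interruption, and the uncontrolled design would present a resulting change in their answers as a level change. This rests on the article's own text.

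The size rests on assumptions. With 10–50% of inappropriate catheters unclear and half of those gaining a listed reason only after training, the apparent relative reduction is 5–25%. The upper end should be read as a bound under strong assumptions, not as a forecast; at the lower end the effect is small. The documents do not support calling the primary result invalid or the direction established. They do support a cheap safeguard at data collection, because the information is lost otherwise.

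**What to change.** In both periods:

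1. Record the Table 1 classification from record and observation before anyone is contacted, with an unresolved category.
2. Flag each case in which staff were contacted, and record the classification after contact.
3. Count a verbal reason as appropriate only if neither the record nor the observation contradicts it.
4. Report, by period, the share of cases contacted and the share reclassified.

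Keep the planned primary analysis and add two sensitivity analyses: (a) the pre-contact classification, with unresolved cases counted as inappropriate; (b) contacted cases excluded. Read both alongside the catheter days already collected.

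Do not make analysis (a) a condition for claiming an effect. It ties the outcome to the quality of documentation, which education and feedback may themselves improve after the interruption. That would create a similar step with no catheter removed.

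Cost: one or two extra fields on the data form, extra model runs, and a sensitivity result that may be less favourable than the primary one.

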### De-implementation strategy

We will use a bundle of interventions (Table 4), since it is known that multiple and well-organized interventions result into better improvements. The main intervention is the dissemination of the list of appropriate indications (Table 1), which will restrict the insertion of urinary and intravenous catheters by physicians and nurses. The recommendation will be to remove the catheters without or with an expired valid indication. A local ‘champion’ (one of the leading physicians) will be appointed to be responsible for the interventions in his or her department. The intervention period will start with a kick-off meeting, where a list of baseline data of the intervention hospital in comparison with the other study hospitals will be presented as a competitive feedback report [33]. If desired, feedback reports per department could be sent by e-mail to local investigators. Thereby two educational meetings about insertion, care and maintenance of urinary and intravenous catheters will be applied to change HCWs behavior. Furthermore, HCWs will be encouraged and reminded to remove inappropriate catheters by posters, pocket cards and e-mail messages. In addition to other studies, patients will be actively supported by education material to participate in their treatment.

**Table 4 Tab4:** De-implementation strategy

Interventions of de-implementation strategy
List of appropriate indications
Local ‘champion’
Kick-off meeting, including competitive feedback report of baseline data
Education meeting for healthcare workers
Education materials (e.g., posters, pocket cards)
Patient education materials
Optional interventions based on baseline data and local conditions per hospital

Subsequently, all impeded and promoted factors of this de-implementation strategy for both HCWs and patients will be evaluated by direct observations and interviews. Additional prevention strategies could be applied based on these affecting factors and local conditions in the different hospitals.

If this de-implementation strategy prove to be effective, persistent awareness of the local ‘champion’ in combination with recurrent surveillance of the appropriate use of catheters and catheter-related infections will improve the sustainability. Thereby the de-implementation rule “No indication = Remove catheter” will be recommended in national guidelines and local protocols.

### Sample size

The sample size is based on the objective of a 25–50% reduction in the number of invalid indications for both urinary and peripheral intravenous catheters, with a power of 80% and an alpha of 0.05. We excluded CVCs in the sample size, since the use of CVCs in the internal medicine and subspecialties departments is infrequent, but we will include all patients with a CVC in the study. We used the incidence of inappropriate use of the catheters from previous results in similar healthcare systems, which is 40% in urinary catheters [2, 20] and 50% in PIVC [13]. This results in 91–376 patients with a urinary catheter, and 66–284 patients with a PIVC. Correlating for 10–15% missing data the sample size is set to respectively 105–410 and 75–300 patients in both pre- and post-intervention group. This will result in a total sample size of 210–820 patients with a urinary catheter and 150–600 patients with a PIVC. We aim to include this number of patients in each hospital to evaluate the effect of the interventions in each individual hospital.

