## Background

Healthcare-associated infections (HAIs) are associated with an increased mortality, a longer duration of hospital stay, which results into an increase in substantial costs. The use of invasive medical devices (e.g., urinary catheters, peripheral intravenous catheters (PIVCs) and central venous catheters (CVCs)) are important risk factors for the development of HAIs, which have prevalence of 7.1% measured in a combined point prevalence survey in Europe [1]. So an efficient way to reduce HAIs is to avoid insertion of catheters without an appropriate indication and to reduce the number of catheter days.

In general hospitals 15–25% of patients have an indwelling urinary catheter during their hospital stay. Urinary tract infections are accountable for 40% of all nosocomial infections in Western world hospitals, and 71–80% of these patients had a urinary catheter [2–4]. Nevertheless, the incidence of unwarranted placement of urinary catheters in hospitalized patients is 14–65% [5–10].

PIVCs are the most frequently used invasive medical devices in hospitalized patients. However, 25–56% of the PIVCs inserted in the Emergency Department are inappropriate or even unused [11–16]. In a recent study of internal medicine departments in Spain 81.9% of the patients had one or more PIVCs, of which 19% were no longer necessary [17]. A PIVC can cause serious adverse events, with an incidence rate of catheter-associated bloodstream infection of 0.1% (0.5 per 1000 catheter days) [18].

Central line-associated bloodstream infections (CLABSIs) are a major problem in intensive care units (ICUs). A meta-analysis shows that implementation of central line bundles to reduce the incidence of CLABSIs are effective and cost saving in ICUs [19].

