### Study design and setting

The study design is a multicenter, prospective interrupted time series (Fig. 1), which will take place in seven hospitals in the Netherlands (three university and four general hospitals). We aim to reduce 25–50% of the catheters without an appropriate indication by a de-implementation strategy of multiple interventions. The clinical data collection will be once per 14 days during 8 months in both the pre- and post-intervention period. During these measurement days all patients with a urinary and/or (peripheral and/or central) intravenous catheter inserted during the hospital stay will be enrolled. The de-implementation strategies will start during a transition period of 4 months, while no patients will be included.

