### Patient selection

We will include all patient (≥18 years old) admitted to internal medicine and subspecialties (gastroenterology & hepatology, geriatrics, pulmonology and rheumatology) and all nonsurgical patients admitted to acute medical units, who receive urinary and/or (peripheral and/or central) intravenous catheter. Patients admitted for elective short stay, terminally ill patients and patients who had all catheters prior to admission will be excluded (Fig. 2).

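### The 50% PIVC planning rate is not justified for the enrolled inpatients; over the protocol's own inpatient figures (19–43%), per-hospital power at the stated sizes could fall below 80%.

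*Protocol article*

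**What the plan says.** The Sample size section of the protocol article plans the trial "with a power of 80% and an alpha of 0.05". The effect to be detected is a "25–50% reduction in the number of invalid indications for both urinary and peripheral intravenous catheters". For the baseline it uses a published rate of inappropriate use, "which is 40% in urinary catheters [2, 20] and 50% in PIVC [13"]. The reason given for this choice is that the figures are "previous results in similar healthcare systems". For PIVCs this gives 66 to 284 patients per period, raised to 75 to 300 for missing data. The section aims for these numbers in each hospital, so that each hospital's effect can be evaluated.

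The Background covers reference 13 in this statement: "25–56% of the PIVCs inserted in the Emergency Department are inappropriate or even unused [11–16"]. For internal medicine departments in Spain it reports that "81.9% of the patients had one or more PIVCs, of which 19% were no longer necessary [17"]. The section on earlier intervention studies adds two pre-intervention figures: 43% inappropriate PIVC use on internal medicine wards, and 22.9% unnecessary peripheral and central lines in a general hospital.

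Under Patient selection, eligible patients are adults admitted to internal medicine and its subspecialties, plus nonsurgical patients on acute medical units. They are surveyed on fixed measurement days during the stay.

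**The concern.** The planning rate and the measured quantity appear to come from different settings. The 50% belongs, by the protocol's own grouping, with PIVCs inserted in the Emergency Department that were inappropriate or never used. The trial measures whether a catheter present in an admitted patient on a survey day has a valid indication. The only reason given for the choice is similarity of healthcare system, which does not address setting or type of measurement. All three inpatient figures in the protocol lie below 50%, and none is used, even as a sensitivity case.

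For a fixed relative reduction, a lower baseline means a smaller absolute difference and a larger required sample. What is at stake is the claim of 80% power within each hospital.

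**Working it through.** **Inputs.** Two-sided alpha 0.05 (the sidedness is not stated, but two-sided reproduces the figures), power 80%, equal periods, relative reductions of 50% and 25%, PIVC baseline 50% (Sample size). Alternative baselines: 19% (Background), 43% and 22.9% (section on earlier intervention studies).

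**Formulas.** With d = p1 − p2, p̄ = (p1 + p2)/2 and S = √[p1(1−p1) + p2(1−p2)]:

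- uncorrected size per period: n₀ = [1.96·√(2p̄(1−p̄)) + 0.8416·S]² / d²
- continuity-corrected size: n = (n₀/4)·[1 + √(1 + 4/(n₀·d))]²
- power at n: set m = (n − 1/d)²/n, then power = Φ{[d·√m − 1.96·√(2p̄(1−p̄))] / S}

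**Reproducing the plan.**

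- 50% to 25%: n₀ = (1.342 + 0.557)²/0.0625 = 57.7; corrected 65.4, so 66, as stated.
- 50% to 38%: corrected 283.8, so 284, as stated. An exact 25% reduction (to 37.5%) gives 262, so the protocol appears to have rounded 37.5% to 38%. At an exact 25% reduction, 284 therefore carries a small cushion (83% power).
- Urinary catheters, 40% to 20% and 40% to 30%: 91 and 376, both as stated.

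**Changing only the PIVC baseline.** Example, 19% to 9.5% with n = 66: d = 0.095; m = (66 − 10.53)²/66 = 46.6; power = Φ[(0.649 − 0.969)/0.490] = Φ(−0.65) = 26%.

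| Baseline | n needed per period, 50% / 25% reduction | Power at 66, 50% reduction | Power at 284, 25% reduction | Power at 284, 50% reduction |
|---|---|---|---|---|
| 50% (plan) | 66 / 262 | 80% | 83% | >99% |
| 43% | 83 / 336 | about 70% | 73% | >99% |
| 22.9% | 187 / 801 | 33% | 36% | 94% |
| 19% | 232 / 1005 | 26% | 29% | 88% |

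Without continuity correction, the third and fourth columns become 76% and 75% at 43%, 41% and 40% at 22.9%, and 34% and 33% at 19%.

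**Missing data.** The recruited totals of 75 and 300 should not be credited as evaluable. With 10–15% missing they leave about 64–68 and 255–270.

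**Pooled.** Seven hospitals at 284 give 7 × 284 = 1,988 per period. Power for a 25% reduction from 19% is then about 98%, under the same simple comparison and ignoring clustering and the segmented regression.

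**The case against.** A reader might infer that the stated PIVC sizes simply do not give 80% power. The documents do not support that, for four reasons.

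- The true baseline is unknown. The 19% counts PIVCs no longer necessary, and the 22.9% mixes peripheral and central lines. This trial calls every indication outside its Table 1 inappropriate, including on criteria of use within 24 hours and expected duration, so its rate could be higher than either.
- The only cited ward figure worded as inappropriate PIVC use is 43%, where the shortfall is modest.
- The upper size keeps about 88% power for a 50% reduction even at 19%.
- Acute medical units are eligible, where Emergency Department data may be more relevant. That reference 13 is an Emergency Department study is itself inferred from a citation range; the source is not at hand.

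These points stand. They make the shortfall conditional, but they do not supply a reason for using 50%.

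Two further inferences should be resisted. Enrolment of patients with a "catheter inserted during the hospital stay will be enrolled", together with the rule that "patients who had all catheters prior to admission will be excluded", might be read as ruling out PIVCs placed in the Emergency Department; no passage says so, and the point here does not need it. Nor does the protocol say that a null result in one hospital would count as failure of the strategy. The design is multicenter, all eligible patients on survey days are enrolled, and the per-hospital number is a target rather than a cap.

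**Conclusion.** The concern holds in conditional form. The 50% rate is not justified for the enrolled inpatients, and every inpatient figure in the protocol is lower. If the true baseline lies between 19% and 43%, per-hospital power at each stated size, for its own target, is roughly 26–70% (50% reduction, 66 evaluable) and 29–73% (25% reduction, 284 evaluable) instead of 80%. The loss is modest at the upper end of that range and serious at the lower end. The pooled comparison is not threatened on this account.

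These figures rest on the simple two-group comparison that reproduces the stated sizes, not on the planned segmented regression, and on reading reference 13 as the Background groups it.

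**What to change.** In the Sample size section:

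1. Justify 50% for internal medicine and acute medical unit inpatients under the Table 1 definition, or replace it with the 19–43% range from the protocol's own sources.
2. Restate per-hospital PIVC power over that range at the planned sizes, using evaluable numbers.
3. State that, if the baseline is near 19–23%, a single hospital with about 284 evaluable patients per period can show about a 50% reduction but not a 25% one, so PIVC conclusions on a 25% reduction rest on the seven hospitals pooled.

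The cost is a few sentences and a short power table. No extra patients are needed. The downside is a less favourable stated power for single hospitals.

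### Two sample-size figures do not follow from the stated inputs: 284 PIVC patients should be 262, and 410 urinary-catheter patients leave room for about 8% missing data, not 10–15%

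*Protocol article*

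**What the plan says.** All the figures stand in one paragraph, Sample size, under Methods and Design of the protocol article.

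- **Basis:** "The sample size is based on the objective of a 25–50% reduction in the number of invalid indications", "with a power of 80% and an alpha of 0.05". The sidedness and the formula are not named.
- **Baseline inappropriate use:** 40% for urinary catheters and 50% for PIVCs.
- **Base sizes:** "This results in 91–376 patients with a urinary catheter, and 66–284 patients with a PIVC".
- **After the missing-data allowance:** "Correlating for 10–15% missing data the sample size is set to respectively 105–410 and 75–300 patients in both pre- and post-intervention group".
- **Totals over both periods:** "This will result in a total sample size of 210–820 patients with a urinary catheter and 150–600 patients with a PIVC".
- **Level at which they apply:** "We aim to include this number of patients in each hospital to evaluate the effect of the interventions in each individual hospital".

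The section does not say which end of each range is the target.

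**The concern.** The paragraph prints its inputs and its results side by side, so it can be checked directly. Two steps do not follow. One of the four base sizes does not come from the formula that gives the other three. One of the enlarged sizes is too small for the missing-data rate named in the same sentence. These figures are the plan's claim to adequate size in each hospital. If the stated missing-data rate occurs, the urinary upper figure falls slightly below the stated power.

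A related matter is one of clarity. A range of effects is matched by a range of sizes, and the paragraph attaches 80% power to the whole. A reader could take 105 or 75 patients per period as enough for any reduction between 25% and 50%, when those figures serve only the 50% end.

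**Working it through.** **Inputs (Sample size section).** Power 80%; alpha 0.05, taken as two-sided because that reproduces three of the four figures and one-sided reproduces none; equal pre and post groups. Urinary: 40% to 20% or 30%. PIVC: 50% to 25% or 37.5%.

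**Formula.** With d = p1 − p2, p̄ the mean of p1 and p2, and q = 1 − p:

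- n0 = [1.96·√(2p̄q̄) + 0.8416·√(p1q1 + p2q2)]² / d²
- n = (n0/4)·[1 + √(1 + 4/(n0·d))]² (continuity-corrected)

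**Step 1: base sizes per period.**

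| Comparison | n0 | n, corrected | Rounded up | Plan |
|---|---|---|---|---|
| Urinary 40%→20% | 81.2 | 90.9 | 91 | 91 |
| Urinary 40%→30% | 355.9 | 375.7 | 376 | 376 |
| PIVC 50%→25% | 57.7 | 65.4 | 66 | 66 |
| PIVC 50%→37.5% | 246.1 | 261.8 | **262** | **284** |

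The last row in full: p̄ = 0.4375, so √(2p̄q̄) = 0.7016 and √(p1q1 + p2q2) = 0.6960. Then n0 = (1.3750 + 0.5857)² / 0.015625 = 246.1, and n = 61.5 × (1 + √1.130)² = 261.8.

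Other two-sided variants for that row give 247 (uncorrected), 243 (unpooled), 259 (unpooled with correction) and 246 (arcsine). One-sided gives 194, or 210 with correction. Fisher's exact test reaches 80% at about 266. None gives 284. The corrected formula does give 283.8, rounded up to 284, for 50%→38%. A rounded post-intervention rate is therefore a plausible source, but that is an inference; the text does not mention 38%.

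**Step 2: missing-data allowance.** Allowance covered = 1 − base/enlarged. Size needed = base/(1 − m), with m = 10% and 15%.

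| Base → stated | Covered | Needed at 10% | Needed at 15% |
|---|---|---|---|
| 91 → 105 | 13.3% | 102 | 108 |
| 376 → 410 | **8.3%** | 418 | 443 |
| 66 → 75 | 12.0% | 74 | 78 |
| 284 → 300 | 5.3% | 316 | 335 |
| 262 → 300 | 12.7% | 292 | 309 |

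The simpler method, base × (1 + m), gives 414–433 for urinary catheters, so 410 falls short at 10% by either method. The corresponding urinary total per hospital is 2 × 418 = 836 to 2 × 443 = 886, against 820.

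**Step 3: power at the stated sizes, for a 25% reduction.** Power = Φ{[(d − c)·√n − 1.96·√(2p̄q̄)] / √(p1q1 + p2q2)}, with c = 1/n for the continuity correction and 0 without it.

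| Per period, one hospital | Corrected | Uncorrected |
|---|---|---|
| Urinary 410, 10% missing (369) | 79% | 81% |
| Urinary 410, 15% missing (348.5) | 77% | 79% |
| Urinary 105, none missing | 28% | 33% |
| PIVC 75, none missing | 28% | 34% |

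For the 50% reduction they are sized for, the base sizes 91 and 66 give 80% corrected, or 84% and 85% uncorrected.

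**The case against.** The case against making much of this is strong on several points.

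- **Most figures are right.** Three of the four base sizes are exact, and 105 and 75 carry allowances inside 10–15%. A reader might infer that the sample-size figures are wrong in general; the paragraph does not support that.
- **The two PIVC slips offset.** Once 284 becomes 262, the figure of 300 covers 12.7% missing and falls short only near 15%. The 5.3% shortfall exists only against the printed 284. The 284 itself errs on the safe side.
- **The effect at 410 is small.** The loss is one to three points of power. On the uncorrected formula, which needs 356, 410 would cover 1 − 356/410 = 13% missing. However, the plan prints 376 as its base, so its own sentence still does not hold.
- **The lower figures are not errors.** The low size belongs to the 50% reduction and the high size to the 25% reduction. Power of about 30% appears only when the smallest size is crossed with the smallest effect, and the plan never does that.
- **Nothing stops enrolment at the lower figure.** Study design and setting fixes measurement at once every 14 days for 8 months per period, enrolling all eligible patients in seven hospitals. A reader might infer that the 25% objective would go essentially untested. That does not follow. Even at the lower figure everywhere, 7 × 105 = 735 urinary and 7 × 75 = 525 PIVC patients per period would give about 98% power for a 25% reduction in a simple pooled comparison, ignoring clustering and the time-series structure.

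All of this stands. What remains is that 284 does not follow from the inputs, that 410 does not carry the stated allowance, and that the paragraph leaves unsaid which figure supports which reduction in a single hospital.

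**Conclusion.** The point holds in a limited form. Two printed figures disagree with the inputs printed beside them. The PIVC base size should be 262, so 284 is about 8% too high. The urinary figure of 410 covers 8.3% missing instead of 10–15%, which leaves 77–79% power with continuity correction (79–81% without) across that range.

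The lower figures are correct for a 50% reduction, but give only about 28–34% power for a 25% reduction when one hospital is evaluated on its own. At hospital level it is therefore the upper figures that support the 25% objective. This says nothing against the power of the seven-hospital analysis.

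The conclusion assumes a two-sided test and the continuity-corrected formula, which the plan does not name but which reproduce 91, 376 and 66 exactly. All power figures are for a simple comparison of two independent proportions, the calculation that the printed sizes imply.

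**What to change.** In the Sample size section:

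1. Replace 284 by 262, and keep 300 with a note that it covers about 12–13% missing data. State the formula and that alpha is two-sided.
2. For urinary catheters, either keep 410 and say that it covers about 8% missing, with about 77–79% power at 15%, or restate the requirement as 418–443 per period (836–886 in total per hospital).
3. State that 105 and 75 per period per hospital are sized for 80% power at a 50% reduction only, and give about 28–34% for a 25% reduction in a single hospital's own evaluation. Name the upper figures as those that support the 25% objective at hospital level.

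If 410 is kept, the cost is wording only. Enrolment follows the measurement calendar, so restating the figures does not in itself call for extra measurement days.
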